# Omission of sentinel lymph node biopsy in patients with clinically axillary lymph node-negative early breast cancer (OMSLNB): protocol for a prospective, non-inferiority, single-arm, phase II clinical trial in China

**DOI:** 10.1136/bmjopen-2024-087700

**Published:** 2024-09-10

**Keywords:** Breast tumours, Breast surgery, Quality of Life, Patient Reported Outcome Measures, Clinical Trial

## Abstract

**ABSTRACT:**

**Introduction:**

Sentinel lymph node biopsy (SLNB) is a standard procedure for patients with clinically assessed negative axillary lymph nodes (cN0) during early-stage breast cancer (EBC). However, the majority of EBC patients have a negative pathological confirmation of the sentinel lymph node (SLN), and axillary surgery is inevitably associated with postoperative complications. Considering that SLNB has no therapeutic benefit, this trial aims to determine the safety of omitting SLNB in patients with cN0 early invasive breast cancer.

**Methods and analysis:**

The OMSLNB trial is a prospective, single-arm, non-inferiority, phase II, open-label study design involving female breast cancer patients with a tumor of ≤3 cm in diameter, who are considered axillary lymph-node-negative based on two or more radiological examinations, including axillary lymph node ultrasonography. Eligible patients will avoid axillary surgery but will undergo breast surgery, which is not limited to breast-conserving surgery. The trial begins in 2023 and is scheduled to end in 2027. The primary endpoint is 3 year invasive disease-free survival (iDFS). The secondary endpoints include the incidence of breast cancer-related lymphoedema, patient-reported outcomes, locoregional recurrence, local recurrence and regional recurrence. It is expected that the 3 year iDFS in patients undergoing SLNB is about 90%, combined with a non-inferiority cut-off of 5%, 80% power, 95% CIs, 0.05 test level, and 10% loss to follow-up rate, the planned enrollment is 311 patients. All enrolled patients will be included in the intention-to-treat analysis.

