## Methods and analysis

### Trial design and setting

This study is a prospective, noninferiority, single-arm, phase II open-label clinical trial conducted at the First Hospital of Nanjing Medical University. Patients with unilateral invasive breast cancer (tumor ≤3 cm) and assessed as cN0 will be eligible for inclusion. The enrolled patients are required to complete two or more imaging tests, including axillary ultrasound assessed as axillary lymph-node-negative, and other tests including MRI, PET-CT and [18F]-FDG PET/MRI. Patients with suspected lymph node metastasis will be directly excluded from enrollment. All patients are required to undergo preoperative coarse needle aspiration or intraoperative mass biopsy for pathologically confirmed invasive breast cancer (regardless of pathological type). Subsequently, surgeons will be required to provide a detailed explanation of the potential benefits and risks associated with the omission of SLNB to eligible patients. Before any surgical procedure is undertaken, patients must provide written informed consent. Following consent, patients will undergo BCS or mastectomy (allowing for breast reconstruction) without axillary surgery, with a postoperative follow-up of 3 years.

This clinical study will be conducted following the relevant provisions of the Declaration of Helsinki, and it was registered at http://www.clinicaltrials.gov (NCT number: NCT05935150). The study was reported according to the Standard Protocol Items: Recommendations for Interventional Trials (SPIRIT) checklist.^29^ The detailed flow chart of the study is shown in figure 1.

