### Clinical intervention and follow-up

After obtaining informed consent, axillary surgery will be omitted for eligible patients, and BCS or mastectomy (allowing breast reconstruction) will be voluntarily selected by the patient under the premise of ensuring therapeutic efficacy. Patients receiving BCS must undergo whole breast irradiation (WBI) after surgery, and postoperative adjuvant therapy and other treatments will be performed according to clinical guidelines.

Multiple timepoints will be established for dynamic follow-up at baseline and up to 3 years postoperatively, with a comprehensive and objective assessment of breast cancer-related lymphoedema (BCRL) using multi-segmental arm circumference measurements and bioelectrical impedance analysis at baseline, 1 week, 1, 3, 6, 12, 18, 24, and 36 months postoperatively, respectively. Patients will be administered a QoL questionnaire using the validated FACT-B (Version 4.0) and Quick DASH at the same time point.^30 31^ BCRL incidence and QoL will be subjectively assessed by patients using patient-reported outcomes (PROs).

Patients who discontinue or withdraw from the trial for any reason during the trial can be treated with disease-specific therapies, including supplemental SLNB, ALND, radiotherapy and other therapies as appropriate, after obtaining informed consent.

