### Endpoints

#### Primary endpoint

The primary endpoint of this trial is 3 year invasive disease-free survival (iDFS), defined as the time from surgery to local recurrence, regional recurrence, distant metastasis, infiltration of the contralateral breast cancer or death from any cause, whichever occurs first.

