### Sample size calculation

In this study, we used PASS software (version 2021) to perform a sample size calculation for a one-proportion non-inferiority test. The sample size was based on the primary endpoint of iDFS. According to the literature exploration and previous research results, it is expected that the 3 year iDFS in patients undergoing SLNB is about 90%. We set the non-inferiority margin at 5%, with a power of 80%, a significance level (α) of 0.05 and a 95% CI. Considering a 10% dropout rate, PASS software calculated the required sample size to be 311 patients.

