### Trial status

The protocol version number and date were V3.0 and 21 May 2023. The study was conceived and designed in 2022. The first patient was enrolled on 28 June 2023, and enrolment is expected to be completed in June 2026. At the time of manuscript submission, the study was in the process of enrolling patients.

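### The stated 2027 end date is incompatible with enrolment to June 2026 plus 3 years of follow-up; closing in 2027 would cut short the 3-year iDFS endpoint and lower its power

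*Protocol article*

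**What the plan says.** The statements that fix the calendar stand in different sections of the protocol article.

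- Abstract, Methods and analysis: "The trial begins in 2023 and is scheduled to end in 2027".
- Trial status: "The first patient was enrolled on 28 June 2023, and enrolment is expected to be completed in June 2026".
- Trial design and setting: surgery without axillary staging, "with a postoperative follow-up of 3 years".
- Clinical intervention and follow-up: "Multiple timepoints will be established for dynamic follow-up at baseline and up to 3 years postoperatively". The listed visits run to 36 months, and Table 1 under Recruitment has a 3-year column.
- Primary endpoint: "The primary endpoint of this trial is 3 year invasive disease-free survival (iDFS), defined as the time from surgery to local recurrence" (the definition then lists the further event types). The clock starts at surgery.
- Sample size calculation: a one-proportion non-inferiority test with an expected 3-year iDFS of about 90%, a 5-point margin, 80% power and α of 0.05. The resulting total is given as follows: "Considering a 10% dropout rate, PASS software calculated the required sample size to be 311 patients".

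The Statistical analysis section names Kaplan-Meier curves for iDFS. No section gives a common cut-off date, shorter follow-up for late entrants, or an end date later than 2027.

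**The concern.** The last patient enters in June 2026 and needs 36 months, so the three commitments (end in 2027, enrolment to June 2026, 3 years per patient) cannot all be kept. If the end date is the one that is followed, late entrants are censored before the time point that defines the primary endpoint.

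The sample size rests on a one-proportion test, which treats 3-year status as known for every evaluable patient. Closing early removes part of that information, so the trial would test its non-inferiority claim with less power than it states. The article makes a later phase III trial conditional on this result, so a false failure to show non-inferiority has a real cost.

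**Working it through.** **1. The plan's own sample size.** Inputs from Sample size calculation: expected 90%, margin 5 points (null value 85%), power 80%, α 0.05. The article does not say whether α is one- or two-sided. With one-sided 5%:

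n = [(1.645·√(0.85·0.15) + 0.842·√(0.90·0.10)) / 0.05]² = 282.1, so 283 evaluable patients.

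283 × 1.1 = 311.3, and 283 / 0.9 gives 315. The planned 311 is reproduced and is not in dispute. Taking 10% off 311 leaves about 280 evaluable patients.

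**2. Calendar.** June 2026 + 36 months = June 2029. On 31 December 2027 the last patient would have about 18 to 19 months of follow-up. Conversely, only patients operated on by 31 December 2024 can reach 36 months by 31 December 2027. This step needs no assumption.

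**3. Share without 36 months of follow-up.** Assumption: even accrual from 28 June 2023 to 30 June 2026 (1,098 days), with surgery at entry. The share that reaches 36 months is the number of days from first entry to (end date − 3 years), divided by 1,098.

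| End date | Days | Reach 36 months | Do not |
|---|---|---|---|
| 31 Dec 2027 | 552 | 50.3% | 49.7% (about 155 of 311) |
| 30 June 2027 | 368 | 33.5% | 66.5% (about 207) |
| 1 Jan 2027 | 187 | 17.0% | 83.0% (about 258) |

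Sensitivity at 31 December 2027, with cumulative accrual (t/T)^k: k = 0.5 to 0.75 (front-loaded) leaves 29% to 40% short of 36 months; k = 1.25 to 2 (slow start) leaves 58% to 75%.

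**4. Power of a Kaplan-Meier test of 3-year iDFS against 85%.** Assumptions: exponential iDFS, even accrual, 280 evaluable patients. With t in years, hazard λ = −ln(S)/3, and C(t) the share of patients whose potential follow-up exceeds t,

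SE² = (S²/n) · ∫₀³ λ / [e^(−λt)·C(t)] dt

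Power = Φ[(0.05 − 1.645·SE at 85%) / SE at 90%]

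| Closure | SE at 90% | Equivalent complete n = 0.09/SE² | Power, one-sided 5% |
|---|---|---|---|
| Mid-2029 (full follow-up) | 0.0179 | 280 | 80% |
| 31 Dec 2027 | 0.0196 | 234 | 72% |
| 30 June 2027 | 0.0216 | 194 | 64% |
| 1 Jan 2027 | 0.0252 | 142 | 51% |

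A simulation of 311 patients with 10% exponential dropout and a complementary log-log lower limit gives about 81% with full follow-up, 73% to 74% at the end of 2027 and 54% to 55% at its start. At one-sided 2.5% the same simulation gives about 70%, 60% and 41%.

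**5. Information and error rate at the cut.** In the simulation about 88% of the iDFS events seen under full follow-up have already occurred by the end of 2027, and about 67% by its start. With a true value of 85%, the Kaplan-Meier test at one-sided 5% rejects about 4% to 6% of the time at a 2027 cut.

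**The case against.** The best defence is that 2027 appears once, in the abstract. The body of the article commits consistently to 36 months for every patient, and nothing schedules the primary analysis in 2027. If the body governs, power is unaffected and the repair is one corrected date. That is a plausible reading, but the article does not state it. A 2027 end would also fit enrolment that closed by the end of 2024, so the documents do not show which date is wrong. The conflict stands.

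The rest of the defence limits the size of the problem, and it is largely right. A reader might infer any of the following, and the documents do not support them:

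- *At least half of the patients cannot be assessed at 3 years.* The article gives no accrual curve. Even accrual puts the share at 49.7% on the last day of 2027, and front-loaded accrual puts it well below half.
- *Most of the endpoint information would be missing.* By the end of 2027 about 88% of the events would already be observed. Kaplan-Meier, which the article names for iDFS, uses the partial follow-up of late entrants.
- *Power would drop to about half at the end of 2027.* A one-proportion test on the roughly 141 patients with full follow-up would do that (about 45% by the exact test, 51% by normal approximation), but no section proposes a complete-case analysis of iDFS.
- *Carrying the last observation forward would count censored patients as event-free and inflate false non-inferiority.* The Missing data and dropouts section does not mention iDFS or administrative censoring, so this would be a separate question.
- *Non-inferiority could not validly be declared from a 2027 cut.* The Kaplan-Meier test roughly keeps its error rate there; what is lost is power.

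**Conclusion.** The contradiction is certain and follows from the stated dates alone: full follow-up runs to mid-2029, about 18 months beyond the latest reading of the end date. Its consequence depends on which date is followed. If the trial closed in 2027, Kaplan-Meier power at one-sided 5% would be about 73% at the end of that year and about 55% at its start, against about 81% with full follow-up, so the planned 80% would not be delivered. This is more than a clerical slip, because the end date bears directly on the primary endpoint. It weakens the estimate of 3-year iDFS; it does not make it impossible or invalid.

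The shares and powers assume even accrual, exponential iDFS with 90% event-free at 3 years, 10% dropout and a one-sided 5% test. A faster early accrual would soften the loss and a slow start would worsen it.

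**What to change.** Reconcile the end date, the enrolment period and the 3-year follow-up wherever they appear. If enrolment closes in June 2026, the end date becomes mid-2029. State that the primary non-inferiority analysis is done after the last patient's 36-month visit.

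If a 2027 cut-off is really intended, say so and give the date, estimate 3-year iDFS by Kaplan-Meier with administrative censoring at that date, and restate the lower power.

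The cost is a corrected date and, on the first option, a later final report. No visit or patient is added, because Table 1 already schedules the 3-year visit.

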**Ethics and dissemination:**

This trial was approved by the Ethics Committee of the First Affiliated Hospital of Nanjing Medical University (No.2023-SR-193). All participants must provide written informed consent to be eligible. The protocol will be described in a peer-reviewed manuscript, and the results will be published in scientific journals and/or at academic conferences.

**Trial registration number:**

NCT05935150.

Strengths and limitations of this studyPatients enrolled in the OMSLNB trial are required to undergo two or more radiological examinations that assess the axillary lymph nodes as negative.The OMSLNB study setting up dynamic follow-up at multiple time points, where objective measures will be used to assess the incidence of postoperative arm morbidity and evaluate the quality of life in conjunction with subjective patient-reported outcomes.This is a single-centre study, mainly considering that not many hospitals in China are equipped to perform [18F]-fluorodeoxyglucose positron emission/magnetic resonance imaging.

## Introduction

 Since the concept of the sentinel lymph node (SLN) was introduced by Krag *et al* scholars in 1993, axillary surgery for breast cancer progressed towards a minimally invasive era.^1^ The Milan trial, the ALMANAC trial and the NSABP B32 study demonstrated that sentinel lymph node biopsy (SLNB) is a landmark advancement in the field of breast surgery.^2^,^4^ These results confirmed that in patients with negative axillary lymph nodes (cN0) in early-stage breast cancer (EBC), the SLNB group was not significantly different from the axillary lymph node dissection (ALND) group with respect to survival prognosis and local control. However, lymphatic circulation in the upper extremities is more severely impaired in ALND patients, which significantly reduces the quality of life (QoL) rather than contributing a therapeutic benefit.^5^,^8^ Currently, SLNB is recommended as the standard axillary management modality for cN0 patients by several international guidelines.^9^,^11^

SLNB has the potential to result in missed diagnoses as false negative rates (FNR) of 5%–10% are commonly reported.^12^ In the pivotal NSABP B-32 trial,^4^ the FNR for SLNB was 9.8%; however, the 8 year overall survival in the SLNB group was as high as 90.3%, which was not statistically different from that in the ALND group (91.8%) [HR=1.2, 95% CI: 0.96 to 1.50, p=0.12]. In addition, the results of the landmark American College of Surgeons Oncology Group (ACOSOG) Z0011 trial indicated that even in the presence of 1–2 SLNs with macrometastases or micrometastases, performing a more extensive ALND did not improve survival for stage T1-2 patients.^13^ Although non-SLN positivity was detected in 27.3% of the patients in the ALND group, there was no significant difference in the rate of axillary recurrence or DFS in patients in the SLNB group compared with those in the ALND group. This was confirmed in other randomised clinical trials.^14 15^ Other studies reported a low 5 year axillary recurrence rate of 0.3%–2.5% after SLNB,^1316^,^19^ and in a recent prospective SOUND study,^20^ the cumulative incidence of 5 year axillary lymph node recurrence in the omitted SLNB group was only 0.7%. Consequently, these otherwise negative axillary nodes and missed nodes do not appear to pose a serious threat to clinical recurrence and survival. The fact that axillary surgery has never been shown to reduce mortality challenges the premise of the therapeutic efficacy of SLNB.

Although SLNB is a minimally invasive surgical procedure for axillary staging, it is still associated with adverse sequelae. In the ACOSOG Z0011 trial,^13^ approximately one-quarter of the patients in the SLNB group had postoperative complications (including wound infection, lymphedema, axillary sensory abnormalities and brachial plexus injury), and lymphoedema was present in 8% of the patients 6 months after SLNB. The incidence of sensory neuropathy in the SLNB group in the IBCSG 23–01 trial was as high as 13%,^14^ whereas the incidence of lymphoedema was 4%. Similarly, the ALMANAC trial reported a 7% incidence of lymphoedema in the SLNB group.^3^ Considering that SLNB is nontherapeutic and primarily performed for axillary staging, SLNB may represent an overtreatment for SLN-negative patients, and omitting SLNB may result in improved QoL.

In recent years, there have been significant improvements in the accuracy of imaging modalities for preoperative noninvasive axillary staging. A combination of imaging techniques is superior to a single imaging technique for the evaluation of axillary lymph node (ALN) status.^21^ Ultrasonography is the method of choice for ALN assessment in patients with breast cancer.^22^ Choi *et al* found that the specificity of ultrasound assessment of nonpalpable metastatic lymph nodes was 88%–98%.^23^ Another recent meta-analysis revealed that [18F]-fluorodeoxyglucose positron emission/magnetic resonance imaging (FDG PET/MRI) had a higher diagnostic performance compared with MRI in detecting ALN metastases,^24^ but another study found no statistically significant difference between PET/MRI and MRI for N stages.^25^ Preliminary data suggest that PET/MRI has the potential to improve the diagnostic performance of ALN staging, but further studies are needed to confirm and expand the current evidence. Although axillary surgery reduces the risk of axillary recurrence through the local control of the axilla, systemic adjuvant therapy and axillary radiotherapy are also effective. Moreover, postoperative adjuvant therapy should be considered based on the biological characteristics of the tumour rather than the number of ALN involved. Breast cancer treatment decisions frequently rely on tumour biology and genetic profiles. Therefore, the assessment of ALN status is becoming less important.

The OMSLNB trial is designed to evaluate the oncological safety of omitting SLNB for patients with clinically axillary lymph-node-negative, EBC. If the omission of SLNB is noninferior to conventional SLNB for improving survival and controlling recurrence, patients can avoid unnecessary surgery and experience improved QoL with reduced arm morbidity.

Several large prospective clinical trials currently underway, including SOUND,^20^ INSEMA^26^ and the BOOG 2013–08 trial,^27^ are attempting to omit SLNB in patients with cN0 EBC. However, a large number of prospective clinical trials are needed to validate this result, and both of these trials and the OMSLNB trial will provide an important rationale for omitting SLNB in patients with cN0 EBC. This has the potential to change the practice of axillary surgery for EBC in the future.

However, our study possesses several distinct advantages compared with mentioned ongoing trials. First, we have established more stringent inclusion criteria to further enhance the diagnostic performance of ALN staging. Second, given the uncertainty of the tumour location and the actual clinical scenario of a relatively low rate of breast-conserving surgery (BCS) in the Chinese population,^28^ the OMSLNB is the first clinical trial in China to include the omission of axillary surgery in EBC patients planned for mastectomy. Furthermore, this study focuses on women in the Asian Chinese region, where the patient population tends to have a younger age of onset compared with Western patients.

Moreover, the OMSLNB trial will also lay a solid foundation for conducting a future phase III clinical trial. And if the current study achieves its non-inferiority endpoint, we will plan to conduct a larger-scale phase III clinical trial in the future to further validate the efficacy and safety of omitting SLNB.

## Methods and analysis

### Trial design and setting

This study is a prospective, noninferiority, single-arm, phase II open-label clinical trial conducted at the First Hospital of Nanjing Medical University. Patients with unilateral invasive breast cancer (tumor ≤3 cm) and assessed as cN0 will be eligible for inclusion. The enrolled patients are required to complete two or more imaging tests, including axillary ultrasound assessed as axillary lymph-node-negative, and other tests including MRI, PET-CT and [18F]-FDG PET/MRI. Patients with suspected lymph node metastasis will be directly excluded from enrollment. All patients are required to undergo preoperative coarse needle aspiration or intraoperative mass biopsy for pathologically confirmed invasive breast cancer (regardless of pathological type). Subsequently, surgeons will be required to provide a detailed explanation of the potential benefits and risks associated with the omission of SLNB to eligible patients. Before any surgical procedure is undertaken, patients must provide written informed consent. Following consent, patients will undergo BCS or mastectomy (allowing for breast reconstruction) without axillary surgery, with a postoperative follow-up of 3 years.

This clinical study will be conducted following the relevant provisions of the Declaration of Helsinki, and it was registered at http://www.clinicaltrials.gov (NCT number: NCT05935150). The study was reported according to the Standard Protocol Items: Recommendations for Interventional Trials (SPIRIT) checklist.^29^ The detailed flow chart of the study is shown in figure 1.

**Figure 1 F1:**
[figure not shown]
Flow chart of the trial.

### Patient and public involvement

The development of the research question and outcome measures was based on the current clinical context in China and the design of ongoing large-scale prospective clinical studies. Surgeons at the research centre will screen clinical information on patients who are prepared for surgical treatment to assess whether they meet the enrollment criteria. Patients who are willing to participate and eligible for enrollment will then be presented with a detailed explanation of the potential benefits and risks of participating in the study, and written informed consent must be provided for those who agree to enrol. Patients and/or the public were not involved in the design, conduct, reporting or dissemination plans of this research and were not directly involved in the recruitment for this study. We do not plan to proactively disseminate the results to study participants. However, the results will be made available to the general public through publication and other means of dissemination. Participants who are interested in the study results may contact the principal investigator for further information.

